## 11. Data Collection and Follow-Up

Data for SCAR will be collected at standardized intervals beginning at hospital admission and continuing through one year postoperatively. The dataset is organized into domains aligned with international cardiac surgery registry standards while incorporating variables relevant to the Saudi healthcare context. Standardized definitions will be used across participating centers to ensure data consistency, facilitate benchmarking, and enable meaningful national and international comparisons. The complete list of domains, time points, and key variables is presented in Table 1.

Follow-up assessments will be performed at 30 days, 3 months, 6 months, and one year after surgery. Outcome ascertainment will be achieved through a hierarchical approach: outpatient clinic visits and hospital electronic medical records will serve as the primary sources of follow-up data, supplemented by review of readmission records and institutional follow-up databases where available. Direct telephone contact will be used when clinic-based or record-based ascertainment is not achievable. A minimum of three documented contact attempts will be made before a patient is recorded as lost to follow-up. Where available, linkage with national mortality records or Ministry of Health administrative databases may be explored to support outcome ascertainment, particularly for mortality endpoints. Participating centers will be encouraged to maintain accurate patient contact information and verify contact details at each follow-up encounter to minimize loss to follow-up.

Patient-reported outcomes will be assessed using validated Arabic and English versions of the EQ-5D and SF-36 instruments. Baseline assessments will be obtained preoperatively and repeated at 3 months, 6 months, and one year postoperatively to facilitate longitudinal evaluation of functional recovery and health-related quality of life. Administration may be performed in a clinic, by telephone, or electronically according to center capability and patient preference, with efforts made to minimize missing responses through standardized administration protocols. Follow-up data will include survival, major adverse cardiac and cerebrovascular events (MACCE), functional recovery, cardiac rehabilitation referral and participation, return-to-work status, and patient-reported outcome measures.

Cardiac rehabilitation data will include referral status, participation, and program completion where available. Return-to-work status will be assessed among eligible patients and interpreted in the context of age, employment status, and retirement status where applicable.

Both isolated CABG and CABG combined with concomitant cardiac procedures will be included within the registry. Procedure type will be recorded prospectively and incorporated into risk-adjustment models, benchmarking analyses, and outcome reporting to account for differences in operative complexity and baseline risk profiles.

## 12. Objectives and Outcomes

SCAR is designed to establish a national platform for evaluating perioperative and long-term outcomes following coronary artery bypass grafting (CABG) in Saudi Arabia. The registry is based on the premise that standardized nationwide collection of detailed perioperative data will enable identification of patient-, procedure-, and institution-related factors associated with adverse outcomes following CABG surgery.

This study aims to evaluate clinical outcomes, perioperative risk factors, long-term recovery patterns, patient-reported outcomes, and institutional variability among patients undergoing CABG surgery across participating centers in Saudi Arabia.

### 12.1. Primary Objective

To determine the association between preoperative risk factors, intraoperative variables, and postoperative clinical outcomes following CABG surgery, including mortality, major adverse cardiac and cerebrovascular events (MACCE), deep sternal wound infection, and unplanned reoperation.

### 12.2. Secondary Objectives

To evaluate perioperative outcomes, including intensive care unit (ICU) stay, duration of mechanical ventilation, hospital length of stay, blood product utilization, and postoperative complications.To determine predictors of postoperative morbidity and mortality in patients undergoing isolated or combined CABG procedures.To assess institutional variability in CABG outcomes using standardized outcome measures and risk-adjusted benchmarking methodologies.To evaluate long-term outcomes, including one-year survival, MACCE, readmissions, return-to-work status, and recovery of baseline functional status following surgery.To assess participation in cardiac rehabilitation programs and their association with postoperative recovery and long-term outcomes.To assess patient-reported quality-of-life outcomes using validated assessment tools.To validate the performance of established international risk prediction models, including EuroSCORE II and the Society of Thoracic Surgeons (STS) risk models, within the Saudi cardiac surgical population.To facilitate multicenter clinical research and quality improvement initiatives through standardized national data collection.

### 12.3. Primary Outcomes

Primary outcomes will include in-hospital mortality, 30-day major adverse cardiac and cerebrovascular events (MACCE), deep sternal wound infection according to Centers for Disease Control and Prevention (CDC) criteria [19], and unplanned reoperation for bleeding, cardiac tamponade, or graft-related technical failure. Thirty-day MACCE will be defined as a composite endpoint of all-cause mortality, stroke, and myocardial infarction. Perioperative myocardial infarction will be defined according to the Type V universal definition [18]. Stroke will be defined as a new focal neurological deficit of presumed vascular origin lasting more than 24 h and confirmed by neuroimaging where available. Unplanned reoperation will be defined as any return to the operating theatre during the index hospitalization for a complication directly related to the index CABG procedure. Acute kidney injury will be defined and staged according to KDIGO criteria [11].

### 12.4. Secondary Outcomes

Secondary outcomes will include ICU and hospital length of stay, duration of postoperative mechanical ventilation, ICU readmission during index hospitalization, all-cause readmission within 30 days, acute kidney injury, and initiation of renal replacement therapy according to KDIGO criteria [11], postoperative arrhythmias requiring intervention, perioperative blood product utilization, and participation in cardiac rehabilitation programs.

Long-term outcomes will include one-year all-cause survival, one-year MACCE, repeat revascularization, return-to-work status or resumption of baseline functional activity, participation in cardiac rehabilitation programs, and longitudinal changes in health-related quality of life. Health-related quality-of-life measures will be assessed using baseline and follow-up EQ-5D and SF-36 patient-reported outcome instruments to facilitate evaluation of recovery trajectories and clinically meaningful changes over time.

A comprehensive data dictionary defining all primary and secondary outcome variables, including standardized definitions, data sources, and adjudication criteria, will be provided to site leads and data entry personnel at each participating center for reference during data collection and registry operations.

## 13. Development of a Saudi CABG Risk Prediction Model

One of the long-term objectives of SCAR is to facilitate validation of existing international risk prediction models and support the future development of a locally derived CABG risk prediction model for the Saudi population. Initially, registry data will be used to evaluate the performance of established risk stratification systems, including EuroSCORE II and the Society of Thoracic Surgeons (STS) risk models, within the Saudi cardiac surgical population. This validation phase will be undertaken as a priority objective once sufficient registry data have been accrued and will precede any consideration of local model development.

Model performance will be assessed using established measures of discrimination and calibration. Discriminatory ability will be evaluated using the area under the receiver operating characteristic curve (AUC) or c-statistic, while calibration will be assessed through calibration plots, observed-to-expected outcome comparisons, and the Hosmer–Lemeshow test or equivalent calibration metrics where appropriate.

Development of a SCAR-derived risk prediction model will be considered only after accrual of a sufficiently large national dataset with adequate outcome event rates to support robust model development and validation. As a minimum threshold, model development will not be initiated until at least 500 outcome events for the primary endpoint of interest have been accrued across participating centers, in accordance with established recommendations for clinical prediction model development. Candidate predictors will include demographic characteristics, comorbid conditions, frailty measures, cardiac disease severity, operative variables, imaging findings, and perioperative laboratory parameters routinely collected within the registry. Variable selection will be guided by clinical relevance, data completeness, and established predictor selection methodologies to avoid overfitting.

Internal validation will be performed using bootstrap resampling with a minimum of 1000 iterations to provide optimism-corrected estimates of model discrimination and calibration. Subsequent temporal validation using later registry data and external validation across participating centers will be undertaken before any consideration of clinical implementation. Model recalibration and updating strategies will be explored as additional data become available over time.

Any resulting model will be intended to complement existing international risk stratification systems rather than replace them. By incorporating local demographic, clinical, and healthcare system characteristics, such a model may improve risk estimation and benchmarking within the Saudi cardiac surgical population.

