## 15. Statistical Analysis

Statistical analyses will be performed using R (version 4.4.2; R Foundation for Statistical Computing, Vienna, Austria) or IBM SPSS Statistics (version 29.0; IBM Corp., Armonk, NY, USA). Continuous variables will be summarized as mean ± standard deviation or median with interquartile range, as appropriate, while categorical variables will be presented as counts and percentages.

The analytical framework is organized into four sequential tiers corresponding to the registry’s maturation. First, primary descriptive analyses will characterize patient demographics, comorbidity profiles, operative variables, and unadjusted outcome rates across the registry. These analyses will be performed from the outset of data accrual and will form the basis of annual national reports. Second, risk-adjusted benchmarking analyses will compare institutional outcomes after adjustment for case-mix using predefined clinical variables and established risk factors, with hierarchical models incorporating center-level random effects to account for clustering of patients within participating institutions. Third, validation analyses will evaluate the performance of existing international risk stratification systems, including EuroSCORE II and the STS risk models, within the Saudi cardiac surgical population. These analyses will be undertaken once a nationally representative dataset of sufficient size has been accrued. Fourth, risk prediction model development will be considered only after the minimum event threshold defined in the Risk Prediction Model section has been reached.

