Within each tier, specific methods will be applied as follows. Comparisons between groups will be performed using Student’s *t*-test, Mann–Whitney U test, Kruskal–Wallis test, chi-square test, or Fisher’s exact test, as appropriate according to variable type and distribution. Time-to-event outcomes, including survival and freedom from MACCE, will be evaluated using Kaplan–Meier methods and compared using the log-rank test. Multivariable analyses will be conducted using regression models appropriate to the outcome of interest, including logistic regression for binary outcomes, linear regression for continuous outcomes, ordinal regression for ordered outcomes, and Cox proportional hazards models for time-to-event analyses. Propensity score methods, including matching and inverse probability of treatment weighting, will be reserved for specific pre-specified comparative sub-studies rather than applied as a general analytical approach.

Missing data will be evaluated routinely throughout the registry. Where appropriate, multiple imputation by chained equations will be used to address missing data, with complete-case analyses performed as sensitivity analyses to assess the robustness of findings. Patient-reported outcomes will be analyzed using validated scoring methodologies for the EQ-5D and SF-36 instruments. Longitudinal changes in patient-reported outcomes will be evaluated using linear mixed-effects models or generalized estimating equations where sufficient follow-up data are available, with minimally important clinical difference thresholds applied to contextualize observed changes.

Interim descriptive analyses may be performed during early registry implementation to evaluate feasibility, data completeness, follow-up performance, and outcome capture. All statistical tests will be two-sided, and a *p*-value of less than 0.05 will be considered statistically significant.

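### Hosmer–Lemeshow is an ill-suited supporting test for the calibration of EuroSCORE II and STS; calibration intercept and slope with confidence intervals would do the job better at almost no cost

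*Protocol article*

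**What the plan says.** Section 12.2 of the protocol article lists as a secondary objective "To validate the performance of established international risk prediction models, including EuroSCORE II and the Society of Thoracic Surgeons (STS) risk models". Section 13 says that registry data will first be used to "evaluate the performance of established risk stratification systems, including EuroSCORE II and the Society of Thoracic Surgeons (STS) risk models". It names the c-statistic for discrimination, and for calibration it says that "calibration will be assessed through calibration plots, observed-to-expected outcome comparisons, and the Hosmer–Lemeshow test or equivalent calibration metrics where appropriate". Hosmer–Lemeshow is thus the last of three tools. It is replaceable by an equivalent and conditional on being appropriate, but it is the only formal calibration test named.

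Section 15 sets a general convention: "All statistical tests will be two-sided, and a" p-value "of less than 0.05 will be considered statistically significant".

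No sample size is given for the validation. Section 15 says "These analyses will be undertaken once a nationally representative dataset of sufficient size has been accrued", and section 13 places it "once sufficient registry data have been accrued and will precede any consideration of local model development". The one numerical floor, "model development will not be initiated until at least 500 outcome events for the primary endpoint of interest have been accrued", applies to building a local model and so does not set a minimum for the validation that comes before it. The article states no number of risk groups, no degrees of freedom and no decision rule for Hosmer–Lemeshow.

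**The concern.** The validation asks whether fixed probabilities, derived elsewhere, are right for Saudi patients. Hosmer–Lemeshow is usually referred to chi-square on g − 2 degrees of freedom, which is the null distribution for a logistic model whose coefficients were fitted to the same patients. For a fixed score the null is close to chi-square on g degrees of freedom, so the usual form rejects too often.

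The test is also an omnibus one. It spreads a uniform error over all the risk groups and returns a p-value that does not say how far predictions are off, or in which direction. With few deaths it can be non-significant while O/E is clearly away from 1. The article does not say which of the two would then carry more weight.

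At stake is how clearly the validation shows whether these scores need recalibration before they supply expected deaths or inform a decision on a local model.

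**Working it through.** The article gives no operating characteristic for this validation, so there is no stated figure to reproduce.

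**Inputs.** From the article: fixed external scores (section 13), a two-sided 5% level (section 15), and operative mortality of 1.9–2.5% for isolated CABG in the STS database (section 1), used only to set the scale. Assumed: 10 equal risk groups, logit-normal predicted risk, and 1,000 to 5,000 patients.

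**Step 1: false rejection of a correct score.** The 95th percentile of chi-square on 8 df is 15.51. P(chi-square on 10 df > 15.51) = 0.115. With 5 groups the same calculation gives 0.167, and with 20 groups 0.090. Simulated values with 10 groups at 1,000–5,000 patients are about 10–15% on 8 df and 5–9% on 10 df.

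**Step 2: 1.5-fold over-prediction, by hand.** Take true mortality 2% and predicted 3%, so O/E = 0.67. Using Poisson variances, a group with E expected deaths has true variance 2E/3 and bias E/3. Its mean contribution to the statistic is 2/3 + E/9. Over 10 groups the mean statistic is 6.67 + (total E)/9. The 5% cut-offs are 15.51 (8 df) and 18.31 (10 df). For overall O − E, the mean z is (O − E)/√E.

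- 1,000 patients (20 deaths against 30 expected): 6.67 + 3.33 = 10.0, the same as the null mean on 10 df; z = −10/√30 = −1.83.
- 2,000 patients (40 against 60): 6.67 + 6.67 = 13.3, below both cut-offs; z = −20/√60 = −2.58.
- 5,000 patients (100 against 150): 6.67 + 16.67 = 23.3, above both cut-offs; z = −50/√150 = −4.08.

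**Step 3: the same error, by simulation (detection rates).**

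| True / predicted risk | Patients | H–L, 8 df | H–L, 10 df | O − E test |
|---|---|---|---|---|
| 2.0% / 3.0% | 1,000 | 8–10% | 3% | 47% |
| | 2,000 | 32–35% | 16% | 81% |
| | 3,000 | 60% | 40% | 94% |
| | 5,000 | 91–93% | 82% | 99% |
| 1.5% / 2.2% | 1,000 | 6% | 3% | 34% |
| | 2,000 | 18% | 8% | 68% |
| | 5,000 | 69% | 50% | 97% |

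At 2,000 patients, Hosmer–Lemeshow on 8 df is non-significant while O − E is significant in about half of the datasets (46–53%). For under-prediction (O/E 1.5, 2,000 patients) the weakness is small: 77% on 8 df and 67% on 10 df, against 84% for a test of the calibration intercept.

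**Step 4: what O/E cannot see.** Suppose average risk is right but the calibration slope is 0.7. O/E then flags a problem in only about 5% of datasets. A slope test detects it in 57–65% at 2,000 patients and 89–96% at 5,000, against 42–44% and 64–76% for Hosmer–Lemeshow on 10 df. These figures depend on the spread of risk. A re-run with a narrower spread (logit SD 0.9) gave 41% against 28% at 2,000 patients and 77% against 50% at 5,000. At 1,000 patients the two tests were about level.

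**The case against.** The defence is strong, and most of it stands.

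- **Degrees of freedom.** A reader might infer that the plan will reject a correct score at more than twice the nominal rate. That follows only if g − 2 is used. The article does not say so, and group number and degrees of freedom are details that an analysis plan commonly holds.
- **Other tools.** A reader might infer that a score overstating deaths by half would pass. The same sentence lists plots and O/E, and O/E catches that error nearly as well as an intercept test: 68% against 71% at 2,000 patients in the lower-risk setting. The large gap lies between Hosmer–Lemeshow and the intercept test. It does not lie between the plan and the proposal.
- **Sample size.** Missing the over-prediction is a small-sample result. At 5,000 patients Hosmer–Lemeshow detects it in about 70–90% of datasets on 8 df, and validation is deferred until the data are judged sufficient.
- **Interpretation.** Nothing in the article says that a non-significant result means good calibration. The 0.05 convention is general and is not a calibration rule.
- **Wording.** The qualifiers attached to the test already permit better metrics. That a condensed article names no slope or interval is not in itself a fault.

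What survives is narrower. The article does name this test for fixed scores. Moving to g degrees of freedom repairs its false-rejection rate but lowers its power further. Neither form says how large the error is or which way it runs. The permission to use something better is not a commitment to do so.

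**Conclusion.** This is an optional but worthwhile improvement. Hosmer–Lemeshow is a poor adjunct for validating fixed external scores: 11.5% false rejection in its usual 10-group form, no estimate of size or direction on any degrees of freedom, and weak detection of 1.5-fold over-prediction at roughly 2,000 patients or fewer when mortality is about 2%. At 2,000 patients the plan's own O/E comparison would usually show that error; at 1,000 it would do so in about half of datasets or fewer.

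The article does not support the stronger conclusion that the validation would reach the wrong answer, because it neither fixes the degrees of freedom nor makes this p-value decisive. The clearest gain from the change is the calibration slope, since O/E is blind to slope error. The sizes rest on assumed mortality, spread of risk, 10 groups and sample sizes, none of which the article states for this analysis.

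**What to change.** In section 13, replace the last item of the calibration list (Hosmer–Lemeshow and its qualifiers) with two estimates for each score: the calibration intercept, from a logistic model with the score's log-odds as offset, and the calibration slope. Report each with a 95% confidence interval. Keep the calibration plot and the O/E comparison, and give O/E a 95% confidence interval. State that calibration is judged from these estimates and intervals, and not from a non-significant p-value.

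The cost is a small wording change, two extra logistic regressions per score on data already being collected, and the loss of one familiar p-value. Section 4 says that recruitment and data collection have not begun, so nothing already done is affected.

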## 14. Electronic Data Management, Security, and Quality Assurance

All registry data will be collected and stored using a secure web-based electronic case report form (eCRF) within the SCAR data platform. The registry infrastructure is designed to support standardized multicenter data collection, longitudinal follow-up, audit functionality, real-time analytics, and secure institutional access across participating centers. The platform incorporates structured electronic forms, predefined variable definitions, automated validation rules, integrated dashboards, and standardized reporting tools to facilitate consistent and reliable data capture. The complete data flow pathway, from patient identification through data entry, quality assurance, and output generation, is illustrated in Figure 2.

Personnel involved in registry data collection and submission will undergo standardized training prior to receiving platform access. Training will cover registry objectives, variable definitions, data collection procedures, outcome ascertainment, and data quality requirements. All users will be provided with a comprehensive data dictionary containing standardized definitions, variable descriptions, and data entry instructions. The data dictionary will also be integrated within the electronic platform to support real-time data entry and validation. Refresher training will be provided at least annually and additionally following any material update to registry procedures or variable definitions.

Each user will receive a unique username and password to access the registry through a secure, encrypted connection (TLS 1.2 or higher). User permissions will be role-based, with access restricted according to assigned responsibilities. Participating centers will have access only to their own institutional data and dashboards, while centralized oversight, audit functions, and national-level analytics will remain restricted to authorized SCAR governance personnel.

The platform will generate a unique registry identification code for each patient, while direct patient identifiers will remain stored only at the local participating center in accordance with institutional privacy policies and applicable national data protection regulations. No identifiable patient information will be included in exported analytical datasets. The central database will maintain a complete audit trail documenting data entry, modification, and export activities. Automated daily backups will be stored on encrypted servers to support long-term data preservation and disaster recovery.

Data quality will be supported through standardized variable definitions, structured eCRFs, predefined dropdown menus, automated plausibility and range checks, mandatory field completion prompts, and validation scripts designed to identify missing or inconsistent entries. Regular centralized data reviews and periodic data quality assessments will be conducted to monitor registry performance.

Source-data verification audits will be conducted on a random sample of 5–10% of submitted cases at each participating center per audit cycle to assess data completeness, accuracy, and consistency between registry records and source clinical documentation. A missing data rate exceeding 10% across mandatory fields, or identification of systematic inconsistency during an audit, will trigger a formal corrective action process comprising targeted retraining, data reconciliation, and a follow-up quality review within 60 days. Participating centers will receive periodic feedback reports summarizing data quality indicators, completeness rates, follow-up capture rates, and identified discrepancies to support continuous improvement.

The registry platform will support automated monitoring of missing data, logical inconsistencies, duplicate records, and outlier values. Data quality metrics, including completeness rates, follow-up capture rates, validation-error frequencies, and audit findings, will be reviewed periodically by the registry governance structure to promote adherence to registry standards and ensure reliable outcome reporting across participating institutions.

